### Study population

We aim to enter all consecutive adult patients who are diagnosed with SE at admission or at any point of the inpatient treatment into the registry.

SE is defined as:

Convulsive, i.e., bilateral tonic-clonic, seizure lasting 5 min or longer [1].SE with prominent motor symptoms other than convulsive SE lasting 5 or more minutes [1].Clinical seizures without prominent motor manifestations lasting 10 min or longer [1, 2].Recurrent seizures without regaining neurological baseline status between them and altogether fulfilling the above mentioned diagnostic time criteria [1, 57].Nonconvulsive or possible electrographic SE (synonymous: ictal-interictal continuum, IIC) diagnosed with EEG according to Salzburg Criteria [58, 59] or American Clinical Neurophysiology Society (ACNS) terminology 2021 (Electrographic SE is defined as an electrographic for ≥ 10 continuous minutes or for a total duration of > 20% of any 60-minute period of recording) [2].

RSE is defined as SE persisting despite administration of at least two appropriately selected and dosed parenteral medications including a benzodiazepine. SRSE is defined as SE persisting or recurring after 24 h or more of treatment with CIVADs [6].

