The overarching goal of the Sustained Effort Network for Treatment of Status Epilepticus/European Academy of Neurology Registry on Refractory Status Epilepticus (SENSE-II/AROUSE) is to harmonize the collection of clinical and EEG data from multiple centers on SE to gain further insight on the management of SE across all its semiologies and etiologies, and to compare second- and third-line treatments and beyond. More specifically, we aim to:

identify risk factors of outcome, refractoriness, super-refractoriness.perform comparative effectiveness studies on third-line treatment and beyond, and on the use of cEEG.collect epidemiological data on rare forms and causes of SE.identify key targets for future randomized controlled trials.

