### Objectives

The main objectives of the study are to assess patient characteristics, treatment modalities, to analyze and collect EEG features and outcome of adults treated for SE and identify predictors of outcome. Data assessed in this study could also identify gaps and opportunities of the management of this medical emergency.

More specifically, the following questions will be addressed:

Which factors determine global outcome at the time of hospital discharge?Which factors are associated with refractoriness and super-refractoriness?What are the efficacy and safety issues associated with each treatment?What are the characteristics of EEG in NCSE and do they carry clinically relevant information?How could we better classify SE taking semiology, etiology, and EEG into account?Are there differences in the pattern of care and outcome between the centers?

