## Discussion

SENSE allowed to include over 1000 patients with SE from 8 centers. The study provided real-life data about SE and in particular refractory SE [54, 55].

It confirmed that a large proportion of first-line treatments was underdosed compared to the guidelines [54]. First-line treatment did not include benzodiazepines in 20% of all cases, 6% and 22% in CSE and non-CSE, respectively. These findings strongly suggest that IV ASMs are less efficacious than benzodiazepines as first-line treatment. Several predictors of SE cessation have been identified, such as a younger age, a lower mRS before SE onset, lower number of comorbidities, benzodiazepine as first-line treatment and a higher cumulative dose of ASMs within the first 30 min [53, 54]. Refractoriness occurred in 55% of patients and was associated with a higher baseline mRS and treatment deviation from guidelines, such as a lower bolus dose than recommended [54]. Unlike other studies, no difference was found comparing etiologies of refractory and non-refractory SE. Variables associated with good outcome in RSE were lower SE Severity Score (STESS) at SE onset, a shorter SE duration, a shorter length of stay and a lack of intubation. More than 70% of refractory SE were treated without airways protection and or mechanical ventilation. Limitations mentioned by the authors were the variability in recruitment of patients through the different centers, who could decrease the cohort homogeneity and potentially impacting on generalizability. Continuous EEGs were not available for most patients, even though it was recommended by several scientific societies [64, 68]. The focus of SENSE was RSE but only a few SRSE were recruited.

SENSE-II/AROUSE will provide high-quality data on SE of all types and severities. We have planned to collect continuous EEG data, if applicable, to alleviate the lack of knowledge about electrographic patterns of NCSE. We will focus on the functional outcome of SE but also on the refractoriness and super-refractoriness to identify potential predictors. Finally, due to lack of studies of third-line treatment and beyond, we plan to perform a comparative effectiveness study based on the collected data.

The evaluation of a large, heterogeneous patient group will hopefully help in clinical decision making in an area where data with higher level of evidence are still lacking.

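### Refractory and super-refractory SE are defined by the treatment received yet serve as outcomes to be predicted, which biases treatment-factor associations

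*Protocol article*

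**What the plan says.** The Study population section fixes both definitions. For refractory SE: "RSE is defined as SE persisting despite administration of at least two appropriately selected and dosed parenteral medications including a benzodiazepine". For super-refractory SE: "SRSE is defined as SE persisting or recurring after 24 h or more of treatment with CIVADs".

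Three places make these states outcomes. The aims at the end of the Background are to "identify risk factors of outcome, refractoriness, super-refractoriness". The Objectives ask: "Which factors are associated with refractoriness and super-refractoriness". The Discussion says the registry will focus on functional outcome but "also on the refractoriness and super-refractoriness to identify potential predictors".

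Under Management protocol, treatment is left to the attending physicians, and an anaesthetic is only one of two options at the third step, the other being a further antiseizure drug.

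On the predecessor registry, the Discussion reports: "First-line treatment did not include benzodiazepines in 20% of all cases". It says that much first-line treatment was underdosed and that refractoriness "was associated with a higher baseline mRS and treatment deviation from guidelines, such as a lower bolus dose than recommended". It also states: "More than 70% of refractory SE were treated without airways protection and or mechanical ventilation".

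The article does not say how SE that persists after inadequate treatment is classed. It does not limit the super-refractoriness question to patients who received CIVADs.

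**The concern.** Each definition has two parts: SE persists, and a specified treatment has been given. As a clinical label that is unremarkable. As an outcome in a predictor analysis it builds part of the exposure into the outcome. An episode that continues after underdosed drugs, or without a benzodiazepine, does not count as refractory until the qualifying treatment has been given. If that never happens, it stays among the non-events, beside episodes that stopped promptly.

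The consequence is directional. Under-treated episodes lose events and adequately treated ones do not, so underdosing and benzodiazepine omission look less harmful than they are, and could look protective. These exposures matter to the registry: the Background describes them as common and linked to poorer outcome.

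Super-refractoriness has the same structure. An episode that persists but is never given 24 h of CIVADs cannot be an event. If such episodes serve as comparators, factors that influence whether a patient is anaesthetised are mixed with factors that make SE resistant to anaesthesia.

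**Working it through.** **The plan's own figures.** Sample size: 3000 × 0.50 = 1500 refractory. The figure of about 150 super-refractory equals 3000 × 0.05, inside the stated 3–10% (90 to 300). Both group sizes reproduce.

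**Refractoriness.** Let p_A and p_U be the probabilities that SE persists with adequate and with inadequate treatment. Let q be the share of persisting under-treated episodes that later meet the treatment conditions and are then coded refractory. Assume that every persisting adequately treated episode is coded refractory.

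- Coded risk, adequate: p_A
- Coded risk, inadequate: p_U × q
- Observed risk ratio = (p_U / p_A) × q = true ratio × q
- The sign reverses when q < p_A / p_U

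None of p_A, p_U or q is in the documents. With assumed persistence of 50% (adequate) and 65% (inadequate), the true risk ratio is 0.65/0.50 = 1.30 and the true odds ratio is (0.65/0.35)/(0.50/0.50) = 1.86.

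| q | Coded risk, inadequate | Observed risk ratio | Observed odds ratio |
|---|---|---|---|
| 1.0 | 0.65 | 1.30 | 1.86 |
| 0.8 | 0.52 | 1.04 | 1.08 |
| 0.77 | 0.50 | 1.00 | 1.00 |
| 0.5 | 0.325 | 0.65 | 0.48 |
| 0 | 0 | 0 | 0 |

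The break-even is 0.50/0.65 = 0.77. For other true risk ratios it is 0.91 (ratio 1.1), 0.83 (ratio 1.2) and 0.71 (ratio 1.4).

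**Super-refractoriness.** Inputs: 1500 refractory and 150 super-refractory (Sample size); fewer than 30% of refractory SE ventilated (Discussion, predecessor registry). Assumption: CIVAD treatment implies ventilation, so ventilation bounds CIVAD use.

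- CIVAD-treated, at most: 0.30 × 1500 = 450
- Refractory, not super-refractory: 1500 − 150 = 1350
- Of these, never given CIVADs: 1500 − 450 = 1050
- Share unable to meet the definition: 1050/1350 = 78%

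Varying the planning rates with the CIVAD share held at 30%:

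- RSE 55%, SRSE 3%: (1650 − 495)/(1650 − 90) = 1155/1560 = 74%
- RSE 50%, SRSE 10%: (1500 − 450)/(1500 − 300) = 1050/1200 = 88%

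Varying the CIVAD share of refractory SE, with 1500 and 150 fixed:

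- 20%: 1200/1350 = 89%
- 60%: 600/1350 = 44%

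The share falls below one half once more than 825 of 1500 (55%) receive CIVADs.

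**Size of a restricted analysis.** With 450 CIVAD-treated, there are 150 events and at most 300 comparators.

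**The case against.** The definitions are cited, accepted criteria, and a separate analysis plan may define risk sets. The article does not name dose or benzodiazepine use as planned predictors of refractoriness, and it does not say that super-refractory cases will be compared with everyone else. Time of SE cessation, which does not depend on treatment adequacy, is already collected. All of this is correct and limits the point. It does not remove it, because the outcome definition is fixed here and, applied as written, it produces the miscoding.

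The prevalence figures are also weaker than they look. The 20% without a benzodiazepine and the frequent underdosing concern first-line treatment only. The definition does not require the qualifying drugs to come first, so such episodes can qualify later. The share that never does is unknown.

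Three stronger readings are tempting and are not supported:

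- *The predecessor must have used a looser definition, because it found lower doses associated with refractoriness.* That association can arise under the strict definition whenever q is high enough (above 0.77 in the example). It is also the only empirical direction in the documents, and it is the opposite of a reversal.
- *The 1500 refractory cases may not materialise.* The definition behind the 50% rate cannot be determined from the article.
- *89% of all comparators (2550 of 2850) are invalid.* That count includes the 1500 non-refractory patients. For a prognostic question asked from onset, episodes that stopped without anaesthesia are proper non-events. The same caution applies within the 78%: only SE that persisted without qualifying treatment causes bias, and its number is not given.

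Finally, the remedies are imperfect. Persistence after the first two drugs given still mixes undertreatment with drug resistance, and restricting to CIVAD recipients introduces selection.

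**Conclusion.** The point holds as a bias built into the outcome definitions. If they are used as written to study treatment factors, associations of underdosing or benzodiazepine omission with refractoriness are pulled towards protective by the factor q. The direction follows from the definition, given that adequately treated persisting episodes are all counted. The size does not, because q is not in the documents. A reversal is possible but not shown: it needs q below 0.77 under the assumed 50% v 65%.

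For super-refractoriness, about 78% of refractory non-SRSE cases (74–88% over the planning rates) could not meet the definition. This rests on ventilation as a proxy for CIVAD use and on carrying a predecessor figure over to this registry. CIVADs given without intubation, or more frequent CIVAD use, would lower the share. An analysis that includes persisting episodes from this group would not separate receiving anaesthesia from resisting it.

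This warrants a change to the planned analyses, not to the clinical definitions.

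**What to change.** Keep the Study population definitions as descriptive labels and add the following. This concerns outcome coding only, not treatment.

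1. For analyses of dose, benzodiazepine use and other treatment factors, use an outcome that does not depend on treatment adequacy: time to SE cessation, or SE persisting after the first two parenteral drugs actually given. Enter dose adequacy and benzodiazepine use as covariates, so that undertreatment is modelled and not hidden in the outcome.
2. For super-refractoriness, add an analysis restricted to CIVAD-treated episodes, and analyse receipt of CIVADs as a separate outcome. Report both alongside any prognostic model from onset.
3. For each endpoint, state who is at risk and how SE persisting without qualifying treatment is coded.

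No new data are needed. Table 1 already holds weight and the times of SE onset and cessation; Table 2 holds drugs, doses, administration times and CIVAD start and stop. The cost is statistical. The restricted analysis has at most about 300 comparators under the ventilation proxy, and it conditions on a treatment decision and on survival to 24 h. Its results should be described as applying to anaesthetised patients only.

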### Inclusion and exclusion criteria

Post-anoxic SE is considered to be distinct from other forms of SE and carries a very specific and generally poor prognosis. Therefore, we will exclude patients with post-anoxic SE. No other exclusion criteria will apply besides age (< 18 years).

### Clinical data

Variables in Tables 1, 2 and 3 will be collected.

**Table 1 Tab1:** Baseline, SE-related and outcome variables; SE: Status Epilepticus; mRS: modified Rankin Scale; ILAE: International League Against Epilepsy; NCSE: non convulsive status epilepticus; EMSE score: Epidemiology Based Mortality Score in Status Epilepticus

**Demographics and premorbid status**	Age at admission, gender, ethnicity Estimated weight on admission. Location at SE onset Date and time of hospital admission Premorbid Clinical Frailty Scale [60] and premorbid mRS [61]
**Health variables**	History of previous seizures/epilepsy, history of SE Relevant known health problems (comorbidities) as found in Charlson comorbidities index [62]
**SE-related variables** General	Date and time of SE onset Refractory and super-refractory SE Date and time of refractoriness and super refractoriness
Semiology	Semiology according the ILAE [1] Worst seizure type according to STESS score [63] Level of consciousness at SE diagnosis or onset
Etiology	Etiology according to the ILAE and according to the EMSE score SE episode fulfilling criteria of New Onset Refractory Status Epilepticus (NORSE) or Febrile Infection-Related Epilepsy Syndrome (FIRES) [7]
**EEG-related variables**	Date of ictal EEG (if applicable) EEG pattern *(according to the ACNS 2021 terminology and Salzburg criteria for NCSE)* [2, 58, 59] EEG findings as classified in EMSE score [50] If NCSE was diagnosed by EEG and clinical response to IV ASM, then the ASMs and the timing and kind of EEG and clinical improvement are documented. Use of cEEG or repeated EEG in management/diagnosis Used EEG-target for CIVAD : seizure suppression, burst-suppression or flat EEG
**Performed diagnosis procedures**	Brain CT or MRI, continuous video-EEG monitoring (cEEG), fluorine-18 fluorodeoxyglucose (FG) brain positron emission tomography (PET) scan, cerebrospinal fluid analysis, antineuronal antibodies research, brain biopsy, therapeutic drug monitoring, Multimodal Invasive Monitoring or other.
**Outcome-related variables**	Date and time of SE cessation and EEG-documentation of SE cessation Date and time of first-time following commands Date of discharge from hospital mRS at discharge and at 30 days after admission (if still hospitalized) At 90 days after discharge: mRS, recurrence of seizure, ongoing ASM therapy Date and cause of death Reason for withdrawal of life support therapies

**Table 2 Tab2:** Treatment-related variables; CIVAD: continuous intravenous anaesthetic drug; EEG: electroencephalography; IV: intravenous; ASM: antiseizure medication; NCSE: nonconvulsive status epilepticus

**First-line Benzodiazepines**	Use of benzodiazepines as first-line treatment Location, date and time of administration Bolus dose and mode of administration
**Second-line and other uses of conventional ASMs and benzodiazepines** (beyond first-line)	Date and time of first administration of any ASM used (including benzodiazepines and conventional ASMs) Bolus dose and mode of administration Maximum daily dose and mode of administration Date and time of last dose applied and reason for discarding the substance. Maximum serum levels of the substances in use (if applicable) Adverse event documentation (if applicable)
**Diagnostic IV ASM trial in IIC**	If NCSE was diagnosed by EEG and clinical response to IV ASM, then the ASMs and the timing and kind of EEG and clinical improvement are documented.
**CIVADs**	Date and time of initiation of any CIVADs Bolus dose, initial and maximal infusion rate Date and time of discontinuation and reason for discontinuation Adverse event documentation (if applicable)
**Inhalational drugs**	Date and time of initiation of any inhalational drugs System of delivery Initial and maximal inhalation rate Date and time of discontinuation and reason for discontinuation.
**Immune therapies**	Use of immune therapy: steroid, intravenous immunoglobulins, plasma exchange, immune-adsorption, cyclophosphamide, rituximab, anakinra, tocilizumab or others. Date and time of initiation and of discontinuation Maintenance dosage and total amount applied
**Additional therapies**	Use of additional therapy: ketogenic diet, vagus nerve stimulation, hypothermia, electroconvulsive therapy and other neurostimulations, neurosurgical procedure or other Date and time of initiation and of discontinuation.

**Table 3 Tab3:** Complications and life support therapies-related variable; ICU: intensive care unit; SE: status epilepticus

**Intubation**	Date and time (if applicable) Reason for intubation (escalation of SE treatment vs. other reason) Duration of intubation
**Vasopressors**	Date and time of initiation of any vasopressor (if applicable) Duration of vasopressors need (hours)
**ICU stay**	Need for ICU stay and duration of ICU stay
**Other**	Other organ support requirement (renal replacement therapies, etc.)

The modified Rankin Scale (mRS) [61] –a global outcome measure of morbidity and impairment -was chosen because of its easy applicability in a large variety of clinical scenarios with neurological diseases.

The premorbid Clinical Frailty Scale [60] was chosen in addition to the mRS for its greater sensitivity to premorbid functional status.

Of note, this study does not require any additional investigation apart from standard treatment and does not interfere in any way with the treatment decisions made by physicians during the inpatient phase. However, the patient will be called 90 days after onset/ discharge, which requires informed consent obtained during the inpatient phase in some countries.

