**Methods:**

Sustained effort network for treatment of status epilepticus/European Academy of Neurology Registry on refractory Status Epilepticus (SENSE-II/AROUSE) is a prospective, multicenter registry for patients treated for SE. The primary objectives are to document patient and SE characteristics, treatment modalities, EEG, neuroimaging data, and outcome of consecutive adults admitted for SE treatment in each of the participating centers and to identify factors associated with outcome and refractoriness. To reach sufficient statistical power for multivariate analysis, a cohort size of 3000 patients is targeted.

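### SE that begins during a hospital stay is enrolled, but the 30-day mRS is counted from admission, so time from SE onset to this assessment depends on where the SE began

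*Protocol article*

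**What the plan says.** The Study population section of the protocol article takes in every consecutive adult "diagnosed with SE at admission or at any point of the inpatient treatment". The Inclusion and exclusion criteria section removes only post-anoxic SE and minors ("No other exclusion criteria will apply besides age (< 18 years"), so SE with in-hospital onset is eligible.

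Table 1, in the Clinical data section, sets the functional measures:

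- Baseline: "Premorbid Clinical Frailty Scale [60] and premorbid mRS [61"]. *Premorbid* is not defined, and no other mRS before the SE is listed.
- In-hospital outcomes: "mRS at discharge and at 30 days after admission (if still hospitalized").
- Late outcome: "At 90 days after discharge: mRS, recurrence of seizure, ongoing ASM therapy".

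No mRS in Table 1 is timed from SE onset. The table does collect the date and time of SE onset, the date and time of admission, the location at SE onset, and etiology.

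**The concern.** An admission anchor suits patients who arrive in SE, because admission and SE onset then nearly coincide. It does not suit a patient who is already in hospital when SE begins. For that patient the 30-day assessment comes sooner after the SE, by exactly the number of days already spent in hospital.

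The same label then covers different lengths of follow-up, and the difference is tied to place of onset. Any factor that varies with place of onset would be compared at unequal times after SE. Use of cEEG may be one. The Management protocol section says some centers also use it to detect delayed cerebral ischemia after subarachnoid hemorrhage, and these are patients already admitted with another acute illness. Use of cEEG is also among the comparative effectiveness aims in the Background. The direction of any distortion is not known from the article: an earlier assessment leaves less time both to recover and to die.

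The undefined term *premorbid* is a related weakness. For in-hospital onset, one site may record function before the admitting illness and another may record function before the SE.

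**Working it through.** **Inputs.** The 30-day anchor (admission, if still hospitalized) comes from Table 1. Eligibility of in-hospital onset comes from the Study population section. The target of 3000 patients comes from the Sample size section. The share with in-hospital onset is not given. The plan states no figure on this point, so there is none to reproduce.

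**Time from SE onset to the 30-day mRS.** Let d be the number of days from admission to SE onset.

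- As written: assessment on hospital day 30, so the time since SE onset is 30 - d.
- Counted from SE onset: time since onset is 30 for everyone, on hospital day 30 + d.

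| d | As written: days after SE onset (30 - d) | Counted from onset: hospital day (30 + d) |
|---|---|---|
| 0 | 30 | 30 |
| 5 | 25 | 35 |
| 12 | 18 | 42 |
| 20 | 10 | 50 |
| 30 | 0 | 60 |
| 35 | -5 | 65 |

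The interval is 30 days only at d = 0, it shortens day for day, and it is negative only for d > 30.

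**How many patients.** This cannot be computed. If the in-hospital share is assumed to lie between 5% and 40%, the number with in-hospital onset is 3000 x 0.05 = 150 to 3000 x 0.40 = 1200. That is a ceiling on the number affected: only those still hospitalized at day 30 have the item, and onset on day 1 or 2 shifts it by only 1 or 2 days.

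**Meaning of the baseline.** Take an invented patient with premorbid mRS 1 before the admitting illness, mRS 4 just before an in-hospital SE, and mRS 4 at discharge.

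- Change from a baseline before the admitting illness: 4 - 1 = 3 points.
- Change from a baseline before the SE: 4 - 4 = 0 points.

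The 3-point decline arises only if the outcome is analyzed as a change score and *premorbid* is read in the first sense.

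**The case against.** The strongest reply is that the 30-day mRS is not the main outcome. The first question under Objectives concerns global outcome at hospital discharge, and the 30-day item applies only to long-stay patients. Onset and admission times are both recorded, so mistimed values can be found. This limits the weight of the point but does not remove it. Identifying a mistimed value does not supply the mRS that was not taken 30 days after SE onset.

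Three stronger readings are tempting, and the article does not support them.

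- A reader might infer that the admitting illness is scored as SE outcome. No section defines outcome as change from premorbid mRS. The Clinical data section describes the mRS as a global measure, and in a prognostic registry the admitting illness is a legitimate determinant of global outcome. Etiology, comorbidities, consciousness at onset and location at onset are all collected for adjustment.
- A reader might infer that outcomes will commonly be measured before the SE. That needs onset after hospital day 30. The Data security and quality assessment section has documentation begin within a few working days of treatment, so such a value would have to be back-filled.
- A reader might see the Abstract's wording, "consecutive adults admitted for SE treatment in each of the participating centers", as a contradiction of eligibility. It is better read as condensed wording, with the Study population section governing.

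It is also fair to say that an mRS for the day before an in-hospital SE would be reconstructed after the event and could be hard to rate in a sedated or postoperative patient. The point does not ask for that field. Separate presentation by place of onset can be left to the analysis plan.

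**Conclusion.** The point holds in a limited form. The stated rule gives the 30-day mRS unequal follow-up after SE, shorter by d days for in-hospital onset, and no later analysis can fully repair this. It affects a secondary outcome in patients with in-hospital onset who are still in hospital at day 30. Their number is unknown, and the 150 to 1200 range above is only an assumed ceiling. The discharge and 90-day mRS are not affected by this anchor.

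The undefined *premorbid* baseline is a clarification. It would carry decline from before the SE into the results only under two conditions: *premorbid* means before the admitting illness, and change from that baseline is analyzed. The article states neither. The change is worth making because it is cheap, not because the main results are shown to be biased.

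**What to change.** 1. In Table 1, count the 30-day mRS from SE onset, or from SE diagnosis where onset is unknown, in either case for patients still hospitalized at that point. The date and time of SE onset are already collected. A date of diagnosis is not listed as such, so the plan should say which recorded date serves.
2. Flag 30-day values already collected from admission for in-hospital cases, so that they are not pooled with values counted from onset.
3. State whether, for in-hospital onset, premorbid mRS means before the admitting illness or before the SE. If it is the former, adjust any analysis of change from premorbid mRS for onset location and etiology.
4. While editing the anchors, reconcile Table 1's late contact with the text below the tables, which says "the patient will be called 90 days after onset/ discharge".

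The cost is one changed label, one definition and one flag. Values already collected for in-hospital cases will not be comparable with the new ones. The item also moves to hospital day 30 + d, so a patient with d = 12 who leaves between hospital days 30 and 42 will have a discharge mRS but no 30-day value.

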### Management protocol

No common management protocol will be imposed on the participating centers. However, most institutions have established a local protocol that is closely related to the most recent guidelines for the management of SE published by the American Epilepsy Society (AES) in 2016 [64].

In general, diagnosis of SE and related conditions is made based on clinical suspicion using physical examination and, where necessary, EEG (including, cEEG).

In most cases, emergency cerebral imaging with CT or MRI as well as standard emergency blood analysis, and CSF analysis if indicated, will be performed. Most frequently, the first treatment step consists of the administration of a benzodiazepine. If unsuccessful, intravenous administration of ASMs such as levetiracetam, valproate, (fos-)phenytoin, or lacosamide follows. As a third step, another ASM is added or anesthetics such as propofol or midazolam. All treatment decisions will remain at the discretion of the attending physicians.

The use of data acquisition sheets for the very early stages SE (Annex; modified from [56]) and ASM trials for IIC, which are already in place in some centers, will be encouraged to facilitate homogenous and complete data collection.

All participating centers perform cEEG for the following indications:

Management of refractory and super-refractory SE.Suspicion of NCSE after a convulsive SE or seizure (lack of return to neurological baseline).

Some participating perform cEEG for additional indications, such as patients unexplained altered mental status, detection of delayed cerebral ischemia in aneurysmal, subarachnoid hemorrhage.

The availability of cEEG is specific to each center, varying from 7 days a week (including Sundays and holidays) to during working hours on weekdays.

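### No reason for starting an anaesthetic is recorded, so airway or ventilator sedation begun while SE is ongoing, or before cessation is documented, cannot be cleanly separated from SE-directed escalation

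*Protocol article*

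**What the plan says.** The article's Clinical data section names Tables 1 to 3 as the variables to be collected. For CIVADs, Table 2 lists "Date and time of initiation of any CIVADs Bolus dose, initial and maximal infusion rate", then "Date and time of discontinuation and reason for discontinuation", and adverse events. The row for inhalational drugs has the same shape: start, delivery, rate, stop and reason for stopping. Neither row has a reason for starting.

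Table 3 does draw this distinction for the airway: "Reason for intubation (escalation of SE treatment vs. other reason". Table 1 records "Used EEG-target for CIVAD : seizure suppression, burst-suppression or flat EEG", the time of SE cessation with its EEG documentation, and "Refractory and super-refractory SE Date and time of refractoriness and super refractoriness".

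The Study population section states: "SRSE is defined as SE persisting or recurring after 24 h or more of treatment with CIVADs". It does not qualify the purpose of the infusion. The Management protocol section describes usual practice as "As a third step, another ASM is added or anesthetics such as propofol or midazolam" and imposes no common protocol on centres. Among the aims in the Background is to "perform comparative effectiveness studies on third-line treatment and beyond, and on the use of cEEG". The Objectives add the efficacy and safety of each treatment and differences between centres.

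**The concern.** In an observational treatment comparison, the indication for treatment is a basic covariate. The drugs named as a third step, propofol and midazolam, can also be given to sedate an intubated patient. Table 3 accepts that intubation may have a reason other than SE, yet the matching question is not asked of the infusion.

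If the two uses cannot be told apart, the CIVAD group mixes patients escalated because earlier drugs failed with patients sedated for another reason. The mix may differ between drugs and between centres. That would distort the third-line comparison, the safety description and the centre comparison. The SRSE group is also exposed, because sites may start the 24 h clock at different infusions. Indication is hard to recover reliably once the episode is over.

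**Working it through.** **1. The plan's own group sizes (Sample size section).** Refractory: 3000 × 50% = 1500, as stated. Super-refractory: 3000 × 3% = 90 to 3000 × 10% = 300; the stated figure of about 150 lies within this range and equals 5%. With about 15 candidate predictors, 150 / 15 = 10 cases per predictor. None of these figures is in dispute.

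**2. What the listed variables can and cannot separate.**

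| Situation at start of the anaesthetic | Listed items that help | Separable? |
|---|---|---|
| SE cessation documented before the infusion | Cessation time against CIVAD start time | Yes |
| SE ongoing, EEG target recorded | EEG target | Mostly; the listed targets are seizure suppression, burst suppression and flat EEG |
| SE ongoing, EEG target blank | Intubation reason | Not cleanly; a blank may mean no target or missing data |
| Cessation undocumented or poorly timed | Intubation reason, EEG target if any | Not cleanly |

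The EEG target item lists no option for no target or sedation only. The intubation reason describes the tube, not an infusion started or continued later for a different purpose. The fourth row is plausible in practice: the Management protocol section says that continuous EEG is available in some centres only in weekday working hours.

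**3. Effect on a treatment comparison.** Let *s* be the share of the CIVAD group given the drug for other sedation, and p_E and p_O the outcome proportions in the escalated and other-sedation patients. The observed proportion is (1 − s)·p_E + s·p_O, so the shift from p_E is s·(p_O − p_E). The document gives neither *s* nor the two proportions. For each 10 percentage points between p_O and p_E (a unit chosen for illustration), an assumed *s* of 5% to 30% shifts the result by 0.05 × 10 = 0.5 to 0.30 × 10 = 3 points.

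Against a non-anaesthetic third-line drug, which is not given for ventilator sedation, the whole shift enters the comparison. Between two anaesthetics or two centres with equal p_E and equal p_O, it is (s_A − s_B)·(p_O − p_E), so it vanishes only if the shares are equal. The sign depends on whether the sedated patients do better or worse, which the document does not tell us.

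**4. Effect on the SRSE group.** Suppose a share *s* of the 150 cases had a first 24 h of anaesthetic given for sedation only (assumed, no rate given) and that time were not counted:

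- s = 5%: 150 × 0.95 = 142.5; / 15 = 9.5 per predictor
- s = 10%: 135; 9 per predictor
- s = 20%: 120; 8 per predictor
- s = 30%: 105; 7 per predictor

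This is the largest loss for each *s*, since some of these patients would still qualify after a later 24 h of SE-directed infusion.

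**The case against.** The strongest reply has three parts.

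**Much is already derivable.** A patient whose SE stopped after one or two drugs and who was then sedated is identified by comparing cessation time with CIVAD start. The EEG target and intubation reason add information, and the intubation reason helps to attribute ventilation complications. This stands, and it limits the point to the last two rows of the table above.

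**The SRSE risk is easily overstated.** A reader might infer that sedation-only propofol or midazolam counts as a treatment step and can by itself make a patient super-refractory. The document does not support that. It neither counts nor excludes such use, and treatment with CIVADs in an SE definition can be read as treatment of SE. SE itself, not merely a seizure, must persist or recur. SRSE status is also entered by the site as its own variable rather than computed from the drug log. What stands is that the site's entry rests on the same unqualified definition.

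**The article condenses a fuller protocol.** The case report form may hold an indication field or coding rule, and data collectors are instructed and supervised. This is fair. But the article presents its tables as the variables to be collected, and they go down to the reason for intubation and for stopping a CIVAD. The missing counterpart is therefore a visible gap, which the sponsor can close by pointing to the field if it exists.

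**Conclusion.** The point holds in a limited form. The listed variables do not identify why an anaesthetic was started, and the available proxies do not resolve infusions begun while SE is ongoing or its cessation is undocumented. The comparisons named in the aims are open to bias of unknown sign, and the 24 h criterion is open to differing site interpretation. No stated figure is wrong and nothing in the text contradicts itself.

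The size cannot be estimated from the document. The 5% to 30% range is an assumption, and on it the cost to the SRSE analysis is at most 0.5 to 3 cases per predictor. It is also tempting to size the problem from the earlier registry's report, in the Discussion, that more than 70% of refractory SE was treated without airway protection, which leaves fewer than 30% of 1500 = 450 intubated. That figure cannot be set against the 150 SRSE cases. Entry to SRSE also needs 24 h of exposure and persisting or recurring SE, and the document gives no rate for either among patients intubated for other reasons.

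This is a cheap improvement worth making while data are being collected, not a flaw that invalidates the registry.

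**What to change.** - Add to Table 2, for each CIVAD and each inhalational drug, a reason for initiation coded as escalation of SE treatment, other sedation, or both.
- Use that field to define the exposure group in the third-line comparison, with a sensitivity analysis that excludes infusions coded as other sedation.
- State, as a data-coding rule, whether sedation-only infusion time enters the 24 h count for SRSE. Which way to decide is for the investigators; what matters is that all sites code it the same way.
- If the case report form already holds such a field or rule, it is enough to say so.

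The cost is one extra REDCap field per anaesthetic and one sentence beside the SRSE definition. The CIVAD group in the sensitivity analysis may become slightly smaller, as may the SRSE group if sedation-only time is not counted. The both category will still leave some attribution open. Care is not affected.
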